### Study population

Study participants are recruited from index case contacts already registered at the ASA who either live in the city of Rio de Janeiro or its metropolitan area. The clientele is mostly comprised of referrals from local health care services (both public and private) and those who arrive spontaneously.

After a leprosy diagnosis (clinical and/or bacteriological and/or histopathological), patients are informed about their clinical form, treatment regimen, mode of transmission, preventive measures, and the importance of presenting their contacts for clinical evaluation. All referrals made by the patient, whether consanguineous or not, household contacts, or those having close familial and/or social ties, are scheduled for a dermatoneurological examination as soon as possible after their index case diagnosis.

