### Statistical analysis

The evaluation of the efficacy of chemoprophylaxis will be based on the occurrence of new cases of leprosy in both groups and will be measured at least at 1 year after the single dose of rifampicin. Over the period of 1 year, three evaluations will be carried out: at baseline, 2 months, and 12 months.

The total number of randomized participants will be analyzed to preserve the safeguards against selection bias and confounding (“intention-to-treat analysis”). An alternative analytical strategy (“per-protocol analysis”) will disregard the data obtained from participants that did not meet the eligibility criteria and did not adhere to either of the intervention regimens or study procedures.

Evaluating the group that adhered to the protocol prevents classification bias that may result from analyzing the participants in the originally allocated group despite their not having followed the specifically planned procedures**.** Any discrepancies in the results of the two analytical strategies will be interpreted in light of the distribution of the baseline characteristics of the participants adhering to the protocol. The balanced distribution of covariates across comparison groups achieved by randomization could be lost as a result of violations in protocol.

The main explanatory variable defined by the study design is the intervention (rifampicin/placebo). Whereas univariate analyses will be performed to describe their baseline characteristics, bivariate analyses will explore the association between intervention and outcomes (response variables). Multivariate analyses (Cox regression) will be conducted to adjust the association estimates (hazard ratio for new cases) for covariates with any imbalance in group distribution. Subgroup analyses of effectiveness (derivatives of the measures of association) according to age, along with the BI and type of cohabitation with the index case, will be carried out.

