### Analyses of outcomes based on immunological and molecular parameters

The quantitative variables analyzed will be those related to the ELISA results on anti-PGL1, LID-1, and IFN-γ. The optical density (OD) of each will be read at 450 nm. PGL-1 samples with OD > 0.25 will be considered positive while LID-1 samples will be considered positive with OD > 0.3. As for IFN-γ, the reading will be performed according to the manufacturer’s recommendations (eBioscience®, San Diego, CA, USA).

Frequency distribution will be constructed to detect asymmetries and the need for scale transformation. The primary analysis will address measures of the central tendencies (mean and median), and those of dispersion (i.e., interquartile range, variance, and standard deviation).

For the continuous variables, paired measurements for each individual will result from blood samples obtained before receiving rifampicin and during the contact visit 2 months after receiving rifampicin and before receiving the BCG vaccine. The results obtained 12 months after the first blood collection will also be submitted to paired analysis with the *t* test comparing the mean values of any changes between the two groups.

The main explanatory variable is intervention (rifampicin/placebo). Bivariate and multivariate analyses (linear regression model) will consider the following major covariates: age group, bacilloscopic index (BI), and type of coexistence with the index case. The response variables will include the anti-LID-1, anti-PGL-1, and IFN-γ measurements on a continuous scale. The effect of the intervention will be evaluated and adjusted for the effects of the other explanatory variables.

Regarding the PCR results (positive/negative), bivariate and multiple analyses (logistic regression model) will include the same previously mentioned explanatory variables: age group, BI, and type of cohabitation with the index case. A 5% significance level will be adopted, and 95% confidence intervals will be constructed for the estimates. Data management will use Microsoft Access®, and statistical analyses will be conducted using SPSS version 22.0 (IBM Corp., 2013).

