### Calculation of sample size

The sample size of this study was calculated on the basis of the primary outcome of the leprosy chemoprophylaxis among contacts using rifampicin associated with BCG vaccine. For the occurrence of this outcome a minimum follow-up time was set at 1 year.

Sample size calculations were based on the proportion of contacts that would likely develop leprosy per intervention group, currently estimated at 5% for the placebo group and 2% for the rifampicin group. With an allocation ratio of 2:1, the difference of 3 percentage points, a statistical power of 80%, and a significance level of 5%, (corrected to 0.025 to account for the interim analysis), the study requires 829 participants in the intervention group and 415 controls for a total 1244 participants. Estimating a 20% loss during follow-up (based on previous ASA data), the total sample size would total 1493 participants (995 in the treatment group and 498 controls). This sample size is appropriate for the analysis of time to failure enabling the study to detect more subtle effects (hazard ratio 0.67). Assuming a 30% seropositivity for PGL-1 among controls, this sample size will provide 85% power to detect an 8 percentage point difference from the treatment group. For 2.5% LID-positive controls, the study has 77% power to detect a 2 percentage point difference. For 35% IFN-γ-based susceptibility the study has an 80% power to detect an 8 percentage point difference. The calculations were performed via PASS11 software [23].

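### The linear and logistic models for the laboratory markers ignore shared index cases, so their intervals for the index case's bacilloscopic index will be too narrow

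*Protocol article*

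**What the plan says.** Under Study population, the article explains that a diagnosed patient is asked to present contacts, and that everyone the patient refers (relatives or not, household or social contacts) "are scheduled for a dermatoneurological examination as soon as possible after their index case diagnosis". The exclusion criteria themselves speak of a cluster of contacts. Several participants can therefore share one index case.

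Under Randomization and blinding, participants are allocated individually, 2:1, in permuted blocks.

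Under Analyses of outcomes based on immunological and molecular parameters, bivariate and multivariate linear regressions for anti-PGL-1, anti-LID-1 and IFN-γ "will consider the following major covariates: age group, bacilloscopic index (BI), and type of coexistence with the index case". The PCR result is analysed by bivariate and multiple logistic regression with the same explanatory variables. A 5% level and 95% confidence intervals for the estimates are promised.

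For the clinical outcome, Statistical analysis says "Multivariate analyses (Cox regression) will be conducted to adjust the association estimates (hazard ratio for new cases"; the covariates are those found to be imbalanced between groups. BI and type of cohabitation appear there as subgroup factors for effectiveness.

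The text names no random effect, GEE, robust variance or other allowance for contacts who share an index case.

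**The concern.** Contacts of one patient share that patient's bacterial load and often a household, so their serology, IFN-γ response and PCR status are likely to be correlated. Ordinary linear and logistic regression treat every contact as an independent observation. For a covariate that is constant across all contacts of an index case, positive correlation makes the ordinary standard error too small. BI is such a covariate. It is read here as the index case's BI, which the subgroup wording supports and which fits the exclusion of contacts who have leprosy at baseline.

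At stake is any statement that contacts of patients with a higher BI have different marker levels or PCR positivity. The interval attached to it would claim more precision than the data hold.

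**Working it through.** **The plan's own figure.** The sample size was computed for independent participants. Inputs from Calculation of sample size: 5% and 2%, 2:1 allocation, 80% power. Using the pooled-variance formula with z = 1.960 (5% two-sided, which equals 2.5% one-sided):

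- Pooled rate: (0.05 + 2×0.02)/3 = 0.03.
- Controls: [1.960×sqrt(0.03×0.97×1.5) + 0.842×sqrt(0.05×0.95 + 0.02×0.98/2)]² / 0.03² ≈ 414.7.
- Treated: twice that, about 829.5.

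This agrees with the article: "the study requires 829 participants in the intervention group and 415 controls for a total 1244 participants". There is no design effect in it. None is needed for the treatment comparison, as shown below.

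**Inputs for the check.** The article gives neither contacts per index case (m) nor ICC, so both are assumed over a range. Blood and lymph samples are not taken from children under 12, so m here means sampled contacts per index case. That is fewer than the enrolled contacts wherever children are included.

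**Formula.** For a covariate constant within index case and clusters of equal size:

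- design effect DE = 1 + (m−1)×ICC;
- ordinary interval width relative to the correct width = 1/sqrt(DE);
- true coverage of the ordinary 95% interval = 2Φ(1.96/sqrt(DE)) − 1.

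Example, m = 4 and ICC = 0.10: DE = 1 + 3×0.10 = 1.30; 1/sqrt(1.30) = 0.877, so the interval is 12% too narrow; 1.96/1.140 = 1.719, so coverage is 91.4% and the false-positive rate 8.6%. For BI, 1244 contacts carry the information of 1244/1.30 ≈ 957.

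| m | ICC | DE | Width ratio | Coverage | False-positive rate | Simulated coverage |
|---|---|---|---|---|---|---|
| 2 | 0.01 | 1.01 | 0.995 | 94.9% | 5.1% | – |
| 2 | 0.05 | 1.05 | 0.976 | 94.4% | 5.6% | 0.9445 |
| 3 | 0.05 | 1.10 | 0.953 | 93.8% | 6.2% | – |
| 4 | 0.10 | 1.30 | 0.877 | 91.4% | 8.6% | 0.918 |
| 4 | 0.30 | 1.90 | 0.725 | 84.5% | 15.5% | 0.8465 |
| 5 | 0.30 | 2.20 | 0.674 | 81.4% | 18.6% | – |
| 6 | 0.30 | 2.50 | 0.632 | 78.5% | 21.5% | 0.797 |

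The last column is from ordinary linear regression on about 1244 simulated contacts, with treatment randomised individually 2:1 and a two-level BI constant within index case (2000 runs per setting). It follows the formula.

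**Other simulated results under the same kind of assumptions.**

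- BI, 2–5 contacts, ICC 0.05–0.30: false-positive rates of about 5–19% for a continuous marker and about 5–12% for a binary outcome. With standard errors clustered on index case, both return to about 4–6%.
- Rifampicin effect: coverage of 0.946 to 0.959 with ordinary standard errors, so no inflation.
- Rifampicin effect by BI (linear model, no treatment effect varying between index cases): ordinary rejection of 3.9–5.7% for the interaction and 4.4–6.1% within a BI subgroup.

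**The case against.** The strongest reply is that BI is not what the trial sets out to estimate. The intervention is the main explanatory variable, BI is there for adjustment, and the BI subgroups are treatment contrasts. For those uses the reply stands: treatment effects, overall and by BI, stay near the nominal level. It does not cover the marker section, which puts BI into bivariate as well as multiple analyses as an explanatory variable and promises intervals for the estimates. Reported as written, those BI intervals are too narrow.

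A second reply is that a journal article names model families and leaves the variance estimator to the full protocol or an analysis plan, neither of which is shown. This stands as a caution. Independence is inferred from the methods named and from the absence of any cluster term; it is not stated. If a fuller document already clusters on index case, one confirming sentence closes the point.

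A third reply is that the size is assumed. That also stands. With 2 contacts and ICC 0.01 the interval is 0.5% too narrow, which is negligible; 19% needs 5 contacts and ICC 0.30.

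A reader might also infer more than the documents support:

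- **That the rifampicin result or the sample size is compromised.** Individual randomisation protects the treatment comparison, so no design effect is called for.
- **That every model is affected.** In the Cox model BI is a covariate only if it is imbalanced between groups, and otherwise defines subgroups of the treatment effect. No Cox model was simulated.
- **That all index-case variables are affected alike.** Type of cohabitation can differ between contacts of the same patient, so it is only partly affected.

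**Conclusion.** The point holds for one coefficient, the index case's BI in the linear and logistic models for the laboratory markers. Its ordinary 95% interval is too narrow by a factor of about sqrt(1+(m−1)×ICC). The error is trivial if few index cases contribute more than one or two sampled contacts and correlation is low, and material if clusters of four or five are common and correlation is 0.10 or more.

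This rests on assumed m and ICC, on equal cluster sizes, on reading BI as the index case's value, and on no clustering being specified in a document not shown. It is a minor point for the trial's main conclusion, but worth correcting because the correction costs almost nothing.

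**What to change.** In the section on immunological and molecular parameters, state that standard errors in the linear and logistic models are clustered on index case (robust variance or GEE), and that the reported intervals are the clustered ones. In Statistical analysis, say the same for the Cox model wherever an index-case factor is a covariate. Random effects or shared frailty should not be listed as interchangeable. In the logistic and Cox models they estimate effects conditional on the cluster, and the planned rates imply only about 37 cases (829×0.02 + 415×0.05 = 37.3), too few to estimate a frailty variance well.

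The cost is somewhat wider BI intervals and an index-case identifier in the analysis file. Contact registration implies that this link exists, but the article does not say so outright and it should be confirmed. The sponsor should also confirm that the planned software offers clustered errors for each model. Sample size and data collection do not change.

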### Calculation of sample size

The sample size of this study was calculated on the basis of the primary outcome of the leprosy chemoprophylaxis among contacts using rifampicin associated with BCG vaccine. For the occurrence of this outcome a minimum follow-up time was set at 1 year.

Sample size calculations were based on the proportion of contacts that would likely develop leprosy per intervention group, currently estimated at 5% for the placebo group and 2% for the rifampicin group. With an allocation ratio of 2:1, the difference of 3 percentage points, a statistical power of 80%, and a significance level of 5%, (corrected to 0.025 to account for the interim analysis), the study requires 829 participants in the intervention group and 415 controls for a total 1244 participants. Estimating a 20% loss during follow-up (based on previous ASA data), the total sample size would total 1493 participants (995 in the treatment group and 498 controls). This sample size is appropriate for the analysis of time to failure enabling the study to detect more subtle effects (hazard ratio 0.67). Assuming a 30% seropositivity for PGL-1 among controls, this sample size will provide 85% power to detect an 8 percentage point difference from the treatment group. For 2.5% LID-positive controls, the study has 77% power to detect a 2 percentage point difference. For 35% IFN-γ-based susceptibility the study has an 80% power to detect an 8 percentage point difference. The calculations were performed via PASS11 software [23].

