Cox regression is used to estimate the conditional hazard ratio and the survival function based on longitudinal data from a dynamic cohort of individuals under surveillance for different periods. The hazard ratio estimates the magnitude of the association between chemoprophylaxis and leprosy. The measurement takes into account the different time periods that have elapsed between exposure (treatment/placebo) and the outcome (illness) for each participant until disease develops or follow-up is discontinued [20]. The survival curve will be required to handle open and continuous recruitment as well as censorship, and the survival rates can be estimated by conditional probability according to the strategy proposed by Kaplan and Meier. The statistical significance will be assessed by the Log-Rank test [21].

For all the analyses, a 5% significance level will be adopted, and 95% confidence intervals constructed for the estimates.

An interim analysis will be conducted at the end of the third year of the study to evaluate individuals who have had at least 1 year of follow-up. This analysis will verify whether the cessation of participant recruitment is warranted by the data collected thus far and will be an opportunity to revise sample calculations according to the results. Interim analysis will seek evidence of the effectiveness, or lack thereof, of chemoprophylaxis or any clear indications that the postulated effect is so unlikely that recruitment is no longer justified. The assessment will be based on the number of events accumulated thus far and the trend in the difference between comparison groups, and the discontinuation of the trial will be submitted to the Data Monitoring Committee.

The critical level of a *z* score to reject the null hypothesis in the interim analysis will be adjusted to 2.782 (*p* = 0.005) in line with the O’Brien-Fleming protocol [22]. The conservative criterion in the interim analysis protects the study from the often-misleading results obtained from smaller samples.

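### The 829 + 415 sample size is the ordinary two-sided 5% result: the stated correction to 0.025 for the interim analysis is not in it, and 0.025 conflicts with the analysis section

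*Protocol article*

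**What the plan says.** In the protocol article, under Calculation of sample size, the event proportions are "currently estimated at 5% for the placebo group and 2% for the rifampicin group". The design uses 2:1 allocation and aims for 80% power. The 5% level is described as "corrected to 0.025 to account for the interim analysis), the study requires 829 participants in the intervention group and 415 controls", which makes 1244 in all. That number is then raised to 1493 for a 20% loss. The section does not say whether the level is one-sided or two-sided.

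Under Statistical analysis, two other statements bear on the level. The first is general: "For all the analyses, a 5% significance level will be adopted, and 95% confidence intervals constructed for the estimates". The second concerns the single planned interim analysis, where the critical z "will be adjusted to 2.782 (*p* = 0.005) in line with the O’Brien-Fleming protocol". No final critical value is given, and no analysis is described as being tested at 0.025.

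**The concern.** The sample-size sentence names the level, the power, both proportions and the allocation ratio, so the N can be checked directly. Halving the level for an interim look should raise N noticeably. If the printed N is the one that belongs to an uncorrected 5%, the sentence claims a protection against the interim look that the number does not contain.

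Two things are at stake. A reader cannot tell at which level the final test will be run, because one section says 5% with an O'Brien-Fleming interim bound and the other says 0.025. The Statistical analysis section also allows the sample calculations to be revised at the interim, and a revision that starts from a mismatched level, power and N carries the mismatch forward.

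**Working it through.** **Inputs** (Calculation of sample size): p1 = 0.05 (placebo), p2 = 0.02 (rifampicin), k = 2 rifampicin per placebo, power 80% (z = 0.8416).

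**Formula** (pooled-variance two-proportion z test, no continuity correction), controls needed:

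n = [z(α)·A + z(β)·B]² / (p1 − p2)²

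- mean proportion = (0.05 + 2 × 0.02)/3 = 0.03
- A = √(1.5 × 0.03 × 0.97) = 0.20893
- B = √(0.05 × 0.95 + 0.02 × 0.98/2) = 0.23937
- (p1 − p2)² = 0.0009

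**Step 1. Reproduce the plan's figure at two-sided 0.05** (z = 1.9600):
(1.9600 × 0.20893 + 0.8416 × 0.23937)² / 0.0009 = 414.7 controls, 829.5 rifampicin, total 1244.2. This matches 415, 829 and 1244.

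**Step 2. Apply the stated 0.025, two-sided** (z = 2.2414):
(2.2414 × 0.20893 + 0.8416 × 0.23937)² / 0.0009 = 498.4 controls, 996.8 rifampicin, total 1495.2. That is about 251 more than 1244.

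Other formulas at two-sided 0.025 do not rescue the printed N. They need 510 (arcsine), 548 (continuity-corrected) or 606 (unpooled) controls, and none gives 415.

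**Step 3. Power of 415 + 829.** Standard error under the null 0.010259, under the alternative 0.011752; power = Φ[(0.03 − z × 0.010259)/0.011752].

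| Level (two-sided) | z | Power, normal formula | Power, exact enumeration of the z test |
|---|---|---|---|
| 0.05 | 1.960 | 80.0% | 80.9% |
| 0.025 | 2.241 | 72.4% | 73.8% |

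**Step 4. The one-sided reading.** One-sided 0.025 uses z = 1.960, the same as two-sided 0.05, so it reproduces 415 + 829. It would be a correction only if the starting 5% were one-sided. The analysis section points the other way: z = 2.782 has a two-sided p of 0.0054 and a one-sided p of 0.0027, and the article prints 0.005. It also pairs 5% with 95% intervals.

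**Step 5. What the interim rule implies for the final level.** The article gives neither the final bound nor the information fraction at the interim, so this step rests on an assumption: two looks, the interim at about half the information. In the O'Brien-Fleming shape the final bound is the interim bound divided by √2, so 2.782/1.4142 = 1.967 (two-sided level 0.0492). The other commonly tabulated two-look value, 1.977, gives 0.0480.

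- z = 1.967: Φ[(0.03 − 1.967 × 0.010259)/0.011752] = 79.8%
- z = 1.977: Φ[(0.03 − 1.977 × 0.010259)/0.011752] = 79.6%

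A bound that needs no timing assumption: spending 0.0054 at the interim leaves at least 0.05 − 0.0054 = 0.0446 for the final test while overall error stays at 5%. At 0.0446 (z = 2.008) the same formula gives about 78.8%. The stated interim rule therefore never requires a final level near 0.025.

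**The case against.** The strongest reply is that nothing in the article is tested at 0.025. The figure appears only in the sample-size parenthesis, and the analysis section sets 5% throughout with an interim bound that costs very little. Under that rule 1244 evaluable participants have close to 80% power, so the design is sound and only a parenthesis is wrong. This stands, and it limits the point. A reader might infer that the trial's true power is 72-74%. The documents do not support that unless the final test is two-sided at 0.025, which the analysis section does not say.

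A second reply is that sidedness is unstated and one-sided 0.025 gives exactly the claimed 80%. That is arithmetically right, and on that reading level, power and N agree. What remains wrong is the description: under the article's own two-sided convention it is no interim correction.

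A third reply is that the enrolled 1493 (995 + 498) reaches 80.0% at two-sided 0.025, and that all randomized participants are to be analysed. The sample-size section, however, assigns the step from 1244 to 1493 to a 20% loss, so the same participants cannot also pay for a stricter level. Whether that loss allowance is itself adequate is a separate matter and is not counted here.

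Finally, the planned test is log-rank or Cox with follow-up beyond 12 months for many participants. The two-proportion calculation checks the planning figure; it is not the power of that analysis.

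**Conclusion.** The statement is wrong as written. The 829 + 415 is the uncorrected two-sided 5% result, and the claimed correction to 0.025 is not in it on either reading of sidedness. At two-sided 0.025 the stated inputs require about 1495 evaluable participants instead of 1244, and 829 + 415 gives about 72% power by the normal formula or 74% by exact enumeration. The 0.025 also conflicts with the 5% level and O'Brien-Fleming bound in the Statistical analysis section.

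The finding concerns incompatible statements of level, power and N. It does not establish a real power deficit: under the interim rule as written, and assuming two looks with the interim at about half the information, power at 1244 evaluable is about 79.6% to 79.8% on the article's own event proportions. The arithmetic in steps 1 to 3 rests only on stated inputs and the usual pooled formula. The two-sided convention is inferred from the analysis section, and the final level of 0.048 to 0.049 is an assumption.

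**What to change.** In Calculation of sample size, remove the parenthesis about 0.025 and state that 829 + 415 was computed at a two-sided 5% level. In Statistical analysis, state the O'Brien-Fleming final critical value, the information fraction it assumes, and the power of 1244 evaluable participants at that level. With the interim at about half the information this would read as a final level of about 0.048 to 0.049 and power of about 79.6% to 79.8%; the sponsor should insert its own values if the planned fraction differs.

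If the sponsor does intend a two-sided 0.025 final test, say so in both sections and restate the power of 829 + 415 as about 72-74%, or raise the evaluable number to about 1495.

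The first route costs a sentence or two of wording and no participants. Restating the power under the second route also needs no participants; keeping 80% there would need about 251 more evaluable.

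### The 20% loss allowance multiplies 1244 by 1.2 instead of dividing it by 0.8, so 1493 randomised covers a loss of 16.7%, a minor shortfall

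*Protocol article*

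**What the plan says.** All the inputs are in the protocol article under Calculation of sample size. The event proportions are "currently estimated at 5% for the placebo group and 2% for the rifampicin group", with 2:1 allocation and 80% power. On that basis "the study requires 829 participants in the intervention group and 415 controls for a total 1244 participants". The next step is the loss allowance: "Estimating a 20% loss during follow-up (based on previous ASA data), the total sample size would total 1493 participants", split as "995 in the treatment group and 498 controls". No other adjustment is stated between 1244 and 1493.

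Three other places affect what a lost participant means in this trial:

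- Statistical analysis: the main analysis is by intention to treat on everyone randomised, with a per-protocol analysis as the alternative.
- Follow-up (text after Fig. 1): cases diagnosed elsewhere are sought in the national leprosy database (SINAN). Contacts found neither there nor at the study clinic are counted as free of disease.
- Statistical analysis: Kaplan-Meier, log-rank and Cox methods are used, so partial follow-up counts.

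**The concern.** A loss allowance should leave the required number after the expected loss. A follow-up loss rate, here taken from the clinic's own earlier data, is a fraction of those enrolled. The number to randomise is therefore the required number divided by one minus the rate. Multiplying by one plus the rate always gives too few, and at 20% the gap is about 4%.

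At stake is whether the published recruitment target delivers the stated power under the stated loss. The figure also matters because the article makes the interim analysis an occasion to revise the sample size. A revision that starts from 1493 as if it covered a 20% loss would carry the slip forward.

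**Working it through.** **Inputs** (Calculation of sample size): proportions 0.05 and 0.02; rifampicin to placebo 2:1; power 80%; required 829 + 415 = 1244; loss 20%; target 995 + 498 = 1493.

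**1. Reproduce the required number.** Pooled-variance test of two proportions, two-sided 5%, no continuity correction. The pooled proportion is (0.05 + 2 × 0.02)/3 = 0.03.

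Controls = [1.960 × √(0.03 × 0.97 × 1.5) + 0.842 × √(0.05 × 0.95 + 0.02 × 0.98/2)]² / 0.03²
= (0.4095 + 0.2015)² / 0.0009 = 414.7

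Twice that is 829.5 and three times is 1244.2. This matches 415, 829 and 1244.

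**2. Reproduce the target.**

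| | Required | × 1.2 | Stated | ÷ 0.8 |
|---|---|---|---|---|
| Rifampicin | 829 | 994.8 | 995 | 1036.25, so 1037 |
| Placebo | 415 | 498.0 | 498 | 518.75, so 519 |
| Total | 1244 | 1492.8 | 1493 | 1555 (1556 summing the rounded arms) |

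All three stated figures match multiplication by 1.2 and none matches division by 0.8.

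**3. What 1493 covers.**
- Loss tolerated: 1 − 1244/1493 = 16.7%.
- Left after 20% loss: 0.8 × 1493 = 1194 (0.8 × 995 = 796; 0.8 × 498 = 398). Shortfall: 1244 − 1194 = 50.
- Extra participants needed at randomisation: 1555 − 1493 = 62, or 4.2% of 1493.

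**4. Power if the lost contribute nothing** (two-sided 5%). Power = Φ[(difference − 1.960 × SE under the null) / SE under the alternative].
- 415/829: (0.03 − 1.960 × 0.01026)/0.01175 = 0.842, power 80.0%.
- 398/796: (0.03 − 1.960 × 0.01047)/0.01200 = 0.790, power 78.5%.

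The cost is about 1.5 percentage points.

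**5. Power if all 1493 are analysed and some cases among the lost are found.** Assumption: the lost 20% carry the same risks as the rest, and a fraction f of their cases is captured. The observed proportions are then 0.05 and 0.02, each multiplied by (0.8 + 0.2f), on 498/995.

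| Cases captured among the lost | Observed proportions | Power, two-sided 5% |
|---|---|---|
| None | 4.0% vs 1.6% | 78.3% |
| Half | 4.5% vs 1.8% | 82.6% |
| All | 5.0% vs 2.0% | 86.1% |

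The article gives no capture rate, so this is a range and not an estimate.

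**The case against.** The strongest reply is that nobody is dropped from this trial's main analysis. Everyone randomised is analysed, cases diagnosed elsewhere are sought in the national database, and time-to-event methods use partial follow-up. Case ascertainment also runs to July 2021 for a cohort recruited from July 2015, so many participants will be at risk for longer than the one-year planning basis. All of this stands as a limit on the consequence: with half of the cases among the lost captured, 1493 already exceeds 80% power. It does not make the sentence right. The section itself treats 20% as a loss to be compensated, and keeping an untraced contact in the denominator as disease-free does not recover a missed case. With no capture, power is 78.3%, much the same as losing those people outright.

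A second reply is that 1493 gives about 80% power at two-sided 0.025 with no loss. That is a coincidence. The text derives 1493 from the loss allowance, and on this reading it would contain no allowance at all.

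Two stronger readings are tempting and are not supported:

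- A reader might infer that the final analysis will rest on only 1194 participants. The analysis population and the database search say otherwise. The figure of 1194 is the number fully followed at 20% loss, not the number analysed.
- A reader might take the section's "a significance level of 5%, (corrected to 0.025 to account for the interim analysis" as a two-sided 0.025 test and charge the loss formula with a fall in power to about 71%. At that level the stated 829 + 415 already has only 72.4%, so most of the gap from 80% comes from how the significance level was used. That is a separate question.

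**Conclusion.** The loss allowance is wrong as written, and the error is minor. The arithmetic is certain, because the inputs and the result stand in the same section and no intermediate step is missing. If lost participants are taken to add no information, the cost is about 1.5 points of power at two-sided 5%. Tracing and partial follow-up may reduce or remove that cost. The power figures rest on a pooled two-proportion test at 5% against 2%, which is the calculation that reproduces 1244. No estimate, test or error rate is affected, and the slip does not show that the trial is materially underpowered.

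**What to change.** Restate the end of the loss calculation in Calculation of sample size. It should say that 1493 randomised (995 + 498) preserves the required 1244 up to a 16.7% loss. It should add that at 20% loss about 1194 (796 + 398) are fully followed, with about 78.5% power at two-sided 5% if the lost contribute no information. If the intention is to cover a full 20% loss, the matching total is 1555, or 1556 as 1037 + 519.

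The restatement costs only wording and changes no procedure. Raising the target would mean 62 or 63 more participants. The planned interim look at the sample size is the natural place to decide that, using the loss and the case capture actually observed.
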